## LIST OF ABBREVIATIONS

| Abbreviation/Term | Definition                                                  |
|-------------------|-------------------------------------------------------------|
| AA                | Arachidonic Acid                                            |
| AE                | Adverse Event                                               |
| ALT               | Alanine transaminase                                        |
| ANCOVA            | Analysis Of Covariance                                      |
| AST               | Aspartate aminotransferase                                  |
| BMI               | Body Mass Index                                             |
| BUN               | Blood urea nitrogen                                         |
| CBC               | Complete blood count                                        |
| CIOMS             | Council for International Organizations of Medical Sciences |
| Cl                | Chloride                                                    |
| CRF               | Case Report Form                                            |
| CRO               | Contract Research Organization                              |
| CVD               | Cardiovascular Disease                                      |
| DHA               | Docosahexaenoic Acid                                        |
| dL                | Decilitres                                                  |
| DPA               | Docosapentaenoic Acid                                       |
| eGFR              | Estimated Glomerular Filtration Rate                        |
| EPA               | Eicosapentaenoic Acid                                       |
| FA                | Fatty Acid                                                  |
| FDA               | Food and Drug Administration                                |
| GCP               | Good Clinical Practice                                      |
| G                 | Grams                                                       |
| h                 | Hour                                                        |
| HDL-C             | High Density Lipoprotein Cholesterol                        |
| ICF               | Informed Consent Form                                       |
| ICH               | International Conference on Harmonisation                   |
| i.e.              | That is                                                     |
| IP                | Investigational Product                                     |
| IRB               | Institutional Review Board                                  |
| K                 | Potassium                                                   |
| Kg                | Killogram                                                   |
| LCPUFA            | Long Chain Polyunsaturated Fatty Acid                       |
| LDL-C             | Low Density Lipoprotein Cholesterol                         |
| M                 | Metre                                                       |
| mg                | Milligrams                                                  |
| mL                | Millilitres                                                 |
| mmHg              | Millimetres Mercury                                         |
| Na                | Sodium                                                      |
| NDI               | Nutrasource Diagnostics Incorporated                        |
| NHP               | Natural Health Product                                      |
| NNHPD             | Non-Prescription and Natural Health Products Directorate    |
| ω-3 FA            | Omega-3 fatty acids                                         |
| OTC               | Over-the-counter                                            |

| Abbreviation/Term | Definition                                  |
|-------------------|---------------------------------------------|
| PI                | Principal Investigator                      |
| RBC               | Red Blood Cell                              |
| REB               | Research Ethics Board (synonymous with IRB) |
| SAE               | Serious Adverse Event                       |
| SF-12             | Short Form-12                               |
| TG                | Triglyceride                                |
| TMF               | Trial Master File                           |
| TPD               | Therapeutics Products Directorate           |
| vWF               | vonWillebrand Factor                        |

## 1 INTRODUCTION

The contents of this document describe the clinical trial procedures that will be followed by the research team and includes information on the access to source data/documents, ethics, data handling and record keeping, as well as procedures for the response to adverse events and/or stopping rules.

### 1.1 Background

The health benefits of omega-3 fatty acids ( $\omega$ -3 FAs) have been extensively examined in many published studies, and these benefits have been observed in patients with a diversity of conditions and diseases, including cardiovascular disease (e.g. atrial fibrillation, atherosclerosis, thrombosis, inflammation, sudden cardiac death, etc.), age-related cognitive decline, periodontal disease, rheumatoid arthritis, etc. (1-9).

These fatty acids may also be beneficial to healthy individuals, in terms of preventative health benefits. In a 2014 published statement, the American Heart Association notes that "*Omega-3 fatty acids benefit the heart of healthy people...*" (10). One of the established biomarkers of omega-3 status, the whole blood OmegaSpot™ is a combined measure of blood eicosapentaenoic acid (EPA) + docosapentaenoic acid (DPA) + docosahexaenoic acid (DHA) levels, and quartiles of this biomarker are inversely linked to risk of sudden death (11). From this biomarker, three other biomarker scores have been derived. The Omega-3 Serum Equivalence Score is inversely associated with heart disease risk reduction (12), the EPA+DHA Serum Equivalence Score is inversely correlated with risk of death from fatal ischemic heart disease (13), and the Omega-3 Red Blood Cell Equivalence Score, also known as the Omega-3 Index, is inversely linked to protection against sudden myocardial infarction (14).

Shahar et al. (1993), reported that the dietary intake of  $\omega$ -3 FAs was inversely associated with blood levels of several coagulation factors, and that one serving per day of fatty fish reduced the levels of fibrinogen, factor VIII, and von Willebrand factor (vWF) by 2.9 mg/dL, 3.3% and 2.7%, respectively (15). The hemostatic profile is an important predictor of cardiovascular disease (CVD); reducing the levels of hemostatic biomarkers such as fibrinogen, Factor VIII and factor vWF may produce a hypocoagulable profile and thus reduce CVD risk in normal individuals.

Sudden cardiac death may be idiopathic in some individuals, but in others it has been linked to electrical instability of the heart or to plaque rupture. Low blood levels of EPA+DHA have been shown to present a risk for sudden cardiac death, and supplementation of the diet with as little as 840 mg/day of EPA+DHA has been proven effective against sudden cardiac death, while an intake of 2-4 g/day assists in reducing levels of pro-inflammatory factors in the blood that may predispose an individual to plaque rupture (16). As a preventive measure, the researchers recommend at least 2 servings of fish per week for a healthy population, or the equivalent intake of EPA+DHA through supplementation.

In a 2012 review, Mozaffarian and Wu noted that the beneficial effects of EPA and DHA, alone or in combination, on various pathways linked to cardiovascular health, warrant an increase in the intake of these long-chain fatty acids (17). They further noted that the reduction of platelet aggregation, improvement in cardiac diastolic filling and arterial compliance, and/or reduction in systemic inflammation, all of which are outcomes of  $\omega$ -3 supplementation, result in a lower risk of atrial fibrillation, fatal cardiac events, and non-fatal cardiovascular events. They further recommend consumption of EPA

and DHA as either fish or fish oils, because of their well-documented beneficial effects on cardiovascular health. These findings corroborate the results of previous reviews, such as the publication by von Schacky and Harris (18). In a review article of both epidemiological and intervention studies,  $\omega$ -3 fatty acid intake was linked to lower levels of CVD, lower blood pressure, heart rate, levels of inflammatory biomarkers and flow-mediated dilation (19). All of these are risk factors for the development of atherosclerosis.

As well as physical health, mental health of healthy individuals, as measured by the Short Form-12 (SF-12) mental health score, has been improved following  $\omega$ -3 supplementation (20). This result is not surprising, given previous research linking lower plasma  $\omega$ -3 fatty acid levels in patients with dementia than in people with normal cognitive function (21). In a study of children in the United Kingdom, those with a lower blood level of DHA exhibited poorer reading ability and poorer working memory performance, even after controlling for sex and socio-economic status (22). They also presented with increased oppositional behaviour, as rated by parents, and greater emotional lability. In an elderly Quebec population, those in moderately good health, as measured by both good physical condition and a lack of cognitive decline, exhibited higher plasma  $\omega$ -3 fatty acid levels than their less healthy counterparts (23).

In a recent comprehensive review of the role of long-chain polyunsaturated fatty acids (LCPUFA) throughout the lifecycle, and of arachidonic acid (AA), EPA+DHA in particular, Jansson and Kiliaan (2014) noted the requirement of neuronal membranes for DHA and AA, particularly in infancy (24). A significant LCPUFA deficiency may lead to schizophrenia, Attention Deficit Hyperactive Disorder, and other neurological disorders. Supplementation with LCPUFA during the perinatal period may improve neural development, and subsequent improvement in cognition, in humans, not only in infancy but throughout life. Throughout the remainder of the lifecycle, the balance between  $\omega$ -6 long chain fatty acids and their  $\omega$ -3 counterparts is important in health maintenance. An  $\omega$ -6: $\omega$ -3 ratio of 1:1 or 2:1 is recommended for optimal health, yet the average ratio in the North American population is estimated to be as much as 10:1 or even 20:1 (25). A 2014 study of the dietary habits of U.S. adults revealed that, in general, North Americans do not meet the recommended  $\omega$ -3 fatty acid intake from foods alone (26). The authors suggest that supplementation may need to be considered, in order to help this population meet their daily needs. Similarly, both the Academy of Nutrition and Dietetics and the American Heart Association suggest a prudent approach in recommending an increased intake of  $\omega$ -3 fatty acids (27, 10). Although both organisations recommend a preference for obtaining  $\omega$ -3 fatty acids through fish consumption, both also recognise that supplementation may also be required in order to meet target values, particularly in at-risk populations.

## **1.2 Investigational Product**

The investigational product, Ultimate Omega®, contains 1000mg fish oil (providing 225mg DHA, 325mg EPA and 90mg other fatty acids). The comparator product, contains 1000mg fish oil (providing 200mg DHA and 300mg EPA).

### **1.3 Risk/Benefits**

#### **1.3.1 Potential Risks**

There are no known risks associated with the use of fish oil at the dosage proposed for this study. Health Canada's monograph for fish oil supports the use of up to 5000mg EPA + DHA in adults per day. Fish oil is known to reduce triglycerides and may increase LDL-C. Individuals using cholesterol-lowering medications or who have significant history of cardiovascular disease will be excluded from this study to mitigate this potential risk.

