| Criteria for Efficacy Evaluation: | 
Red blood cell fatty acid profile;
 
Serum phospholipid fatty acids;
 
Total cholesterol, HDL-C, LDL-C and triglycerides
                                                                                                                                                                                                                                                                                                                                                                                                                                                                                                                                                                                                                                                                                                                                                                                                                                                                                                                                                                                                                                                                                                                                                                                                                                                                                                                                                                                                                                                                                                                                                                                                                                                                                                                                                                      |

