| Criteria for Safety Evaluation:   | 
Adverse Events (AEs)
                                                                                                                                                                                                                                                                                                                                                                                                                                                                                                                                                                                                                                                                                                                                                                                                                                                                                                                                                                                                                                                                                                                                                                                                                                                                                                                                                                                                                                                                                                                                                                                                                                                                                                                                                                                                                                                                                    |

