### **3.1.7 Early Termination/Discontinuation Visit**

Participants may withdraw voluntarily from participation in the study at any time. Subjects will be encouraged to visit the clinic for an early termination visit. At this visit, subjects will be encouraged to return study product and diaries, have blood pressure, heart rate and weight measured and provide a blood sample for analysis of safety parameters (hematology and clinical chemistry).

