### **6.2 Secondary Endpoints**

Secondary outcomes include the red blood cell EPA and DHA after 12 and 16 weeks of supplementation and lipid profile (total cholesterol, LDL-C, HDL-C and triglycerides) after 6 months (24 weeks) of supplementation.

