## **7.4 Hematology and Clinical Chemistry**

Fasting (12 hours) blood samples will be collected at screening (Visit 1) and week 12 (Visit 6) at the end of the treatment period. Samples will be analyzed for complete blood count (CBC) with differential (hemoglobin, hematocrit, white blood cell count with differential, red blood cell count and platelet count), BUN, creatinine, eGFR, AST, ALT, and electrolytes (Na, K, Cl).

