## **8.6 Handling of Missing or Spurious Data**

In the case of outliers or spurious data, that is, data that is not plausible, a rule of plus or minus 3 standard deviations of the mean will be applied to determine if the value should be excluded from analysis. All missing data or data excluded from analysis will be detailed in the final report. Missing values for primary and secondary endpoints at visits 3, 4, 5 or 6 will be imputed with the more recent previously-available value (LOCF, or “last-observation-carried-forward” imputation). No imputation will be performed for any missing daily diary variables, taste and tolerability questionnaire values or missing values of parameters of safety.

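### LDL-C, the laboratory risk the protocol names, is planned only as an efficacy endpoint: no lipid test is specified for early leavers, and carry-forward sets their change to zero

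*Protocol*

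**What the plan says.** - **Risk.** Section 1.3.1 says "Fish oil is known to reduce triglycerides and may increase LDL-C". Its only response is at entry: people on cholesterol-lowering drugs or with significant cardiovascular history "will be excluded from this study to mitigate this potential risk".
- **Role of LDL-C.** The synopsis puts "Total cholesterol, HDL-C, LDL-C and triglycerides" under the efficacy criteria, while its only safety criterion is adverse events. Section 6.2 makes "lipid profile (total cholesterol, LDL-C, HDL-C and triglycerides) after 6 months (24 weeks) of supplementation" a secondary outcome.
- **Safety laboratory panel.** Section 7.4 (Hematology and Clinical Chemistry) lists a blood count with differential and then "BUN, creatinine, eGFR, AST, ALT, and electrolytes (Na, K, Cl". It lists no lipids.
- **Early leavers.** Section 3.1.7 encourages them to attend and "provide a blood sample for analysis of safety parameters (hematology and clinical chemistry".
- **Sampling.** Table 1 and the Diagnostic Tests section place the lipid profile at Visit 1 (screening) and Visit 6 (Day 168) only. Section 8.4 takes Visit 1 as the lipid baseline.
- **Missing data.** Section 8.6 fills missing primary and secondary endpoint values with the latest earlier value. For other variables it says the opposite: "No imputation will be performed for any missing daily diary variables, taste and tolerability questionnaire values or missing values of parameters of safety".
- **Populations.** Under 8.3 the efficacy set needs at least one dose and one post-baseline visit; the safety set needs only the dose.

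**The concern.** The efficacy label decides how LDL-C is collected and how its gaps are filled. As a secondary endpoint with one pre-treatment and one end-of-treatment measurement, it falls under a carry-forward rule that can only return the screening value. Had it been classed as a safety parameter, the same section would have left the gap empty. The label also appears to keep LDL-C out of the blood sample that leavers are already asked to give, so someone who stops before Visit 6 would have no on-treatment value at all.

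At stake is the description of LDL-C change within each arm. Some of the changes summarised would be zeros produced by a rule rather than measurements, and they would come from people who stopped early. A later analysis plan could change the imputation, but it could not recover an LDL-C that was never assayed.

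**Working it through.** **1. The plan's own figure.** Section 8.2 expects 24 completers per arm and 20% attrition: 24/(1 − 0.20) = 30 per arm. This reproduces. It implies 6 leavers per arm, 12 of 60 in all.

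**2. What carry-forward does to LDL-C.** Only two values exist, L1 (Visit 1) and L6 (Visit 6). If L6 is missing, the latest earlier value is L1, because 8.6 does not restrict the carried value to post-baseline measurements. The change becomes L1 − L1 = 0.

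**3. Mean change.** Let d be the completers' mean change and k the leavers per arm who had a post-baseline visit but no Visit 6 LDL-C (0 to 6).

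Mean shown: m = (24 × d + k × 0)/(24 + k) = d × 24/(24 + k)

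**4. Standard error.** With s the completers' SD of change:

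SD² = [23s² + 24(d − m)² + k·m²]/(23 + k), and SE = SD/√(24 + k)

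The documents give neither d nor s. I assume d from 0.10 to 0.30 mmol/L and s = 0.40 mmol/L for illustration. For d = 0.20 and k = 6: m = 0.160; SD² = (3.680 + 0.0384 + 0.1536)/29 = 0.1335; SD = 0.365; SE = 0.365/√30 = 0.0667. Completers alone give 0.40/√24 = 0.0816.

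| k | Share of d kept | Mean (SE), d = 0.10 | Mean (SE), d = 0.20 | Mean (SE), d = 0.30 |
|---|---|---|---|---|
| 0 | 100% | 0.100 (0.0816) | 0.200 (0.0816) | 0.300 (0.0816) |
| 3 | 88.9% | 0.089 (0.0727) | 0.178 (0.0734) | 0.267 (0.0747) |
| 6 | 80.0% | 0.080 (0.0655) | 0.160 (0.0667) | 0.240 (0.0687) |

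The k = 0 row is also what an observed-values rule gives, whatever k is. Mean and SE shrink together: for d = 0.20 their ratio is 0.200/0.0816 = 2.45 without imputation and 0.160/0.0667 = 2.40 with six zeros. The damage is therefore to the estimate and its interval more than to a within-arm test.

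**5. Between arms.** Suppose both arms have the same rise d, similar baselines and 30 people in the efficacy set, with a and b of them missing Visit 6. The expected false difference is d × (a − b)/30. For 6 against 0 it is 0.20d; for 6 against 3, or 3 against 0, it is 0.10d. At d = 0.20 mmol/L these are 0.04 and 0.02 mmol/L. With equal missingness no false difference arises, but a real one is shrunk by the factor in step 3.

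**The case against.** The case on the other side has real substance.

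- **LDL-C is measured.** Completers give a fasting lipid sample at Visit 6 along with the safety tests, and the adverse-event definition in 7.1 covers abnormal laboratory findings. A reader might infer that the named risk goes unmonitored; the protocol does not support that. What it lacks is a planned safety summary of LDL-C and an explicit lipid test for leavers.
- **The planned test compares two fish-oil arms.** It is an analysis of covariance of the Visit 6 value between arms, and within-arm tests are optional in 8.4. A reader might infer that the plan will declare that LDL-C did not rise. No such conclusion is planned. Equally, that test cannot show a rise common to both arms, so the descriptive change by arm is where such a rise would be seen.
- **20% is the upper end.** It needs every expected leaver to have had a post-baseline visit and no Visit 6 LDL-C. The range is 0 to 20%.
- **The early-termination gap rests on a reading.** Section 3.1.7 does not cite 7.4. That section is an imperfect boundary: it omits glucose, which Table 1 lists, and it dates Visit 6 to week 12 instead of Day 168. Still, 3.1.7 uses the title of 7.4, and the synopsis names the lipid profile and the safety parameters as separate items. Omission is the more natural reading, but the text needs clarifying.
- **The population label alone changes almost nothing.** Someone without a post-baseline visit has no LDL-C to contribute to either set unless the early-termination draw includes it.
- **The risk statement is hedged.** Section 1.3.1 opens by saying that there are no known risks at the proposed dosage, and entry is limited to healthy adults aged 18 to 35. This lowers the expected stakes. It does not justify recording zeros for unmeasured values.

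**Conclusion.** The point holds as one of under-collection in leavers and dilution, not of absent measurement. Carry-forward turns each missing Visit 6 LDL-C in the efficacy set into a change of zero, and the specified early-termination tests appear not to include lipids. At the planned attrition, the within-arm mean change is understated by 0 to 20% relative to completers, its standard error is too small because imputed values count as observations, and unequal dropout could create a between-arm difference of up to 20% of the common rise (6 leavers against 0).

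These sizes assume 24 completers per arm and no Visit 6 LDL-C in leavers. The mmol/L figures also depend on assumed values of the rise and SD. Completers are the benchmark for what was observed; the documents do not say what LDL-C would have been in people who stopped. The primary endpoints are unaffected. The change is worth making because it is cheap and the variable is the one laboratory risk that the protocol itself identifies.

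**What to change.** 1. **Sections 7.4 and 3.1.7:** list the lipid profile in the panel and state that the early-termination sample includes it. Record fasting status and time since randomization, and flag non-fasting samples, chiefly because of triglycerides.
2. **Section 8.6:** exempt the lipid variables from having the screening value carried forward to Visit 6, and say whether an early-termination lipid value enters the Visit 6 analysis.
3. **Sections 7 and 8.5:** add a summary of observed LDL-C change from Visit 1 by arm in the safety population, without imputation, with the number measured. LDL-C stays a secondary endpoint.

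**Cost:** one extra assay on a sample already requested, and one extra table. The lipid analysis would rest on observed values, about 24 per arm at planned attrition instead of up to 30. Attendance at early termination is voluntary, so on-treatment values will be recovered only for leavers who come.
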